# List of Abbreviations

*All abbreviations used throughout the protocol must be defined. Add additional abbreviations specific to protocol.*

| **AE** | Adverse Event |
| --- | --- |
| **CFR** | Code of Federal Regulations |
| **CRF** | Case Report Form |
| **CTSC** | Clinical Translational Science Center |
| **DSMB** | Data Safety Monitoring Board |
| **DSMP** | Data Safety Monitoring Plan |
| **FDA** | Food and Drug Administration |
| **GCP** | Good Clinical Practice |
| **HIPAA** | Health Insurance Portability and Accountability Act of 1996 |
| **HRBFA** | Human Research Billing Analysis Form |
| **HUD** | Humanitarian Use Device |
| **ICF** | Informed Consent Form |
| **IDE** | Investigational Device Exemption |
| **IND** | Investigational New Drug |
| **IRB** | Institutional Review Board |
| **PHI** | Protected Health Information |
| **PI** | Principal Investigator |
| **REDCap** | Research Electronic Data Capture |
| **SAE** | Serious Adverse Event |
| **SUSAR** | Suspected Unexpected Serious Adverse Reaction |
| **UIRTSO** | Unanticipated Problem Involving Risks to Subjects or Others |
| **WCM** | Weill Cornell Medicine |

# 1. Study Objectives

## 1.1 Objectives

The primary objective of the study is to demonstrate the efficiency and reliability of selecting gender specific spermatozoa

##

## 1.2 Hypotheses / Research Questions

# 2. Study Design and Rationale

## 2.1 Study Design

Our study aim is to test a simple, reliable, and inexpensive method to attempt selection

of gender specific spermatozoa. Couples will undergo evaluation and treatment according to the standard clinic procedures. Sperm samples provided for infertility treatment will be further analyzed routine semen analysis for volume, concentration, mobility and morphology. Sperm samples will be provided by consenting males undergoing infertility treatment. We will perform a multilayer density gradient utilizing an FDA approved solution, Enhance-S Plus Cell Isolation Media (Vitrolife, San Diego, CA).

This density gradient is also used for our standard semen preparation for intrauterine

insemination. X-bearing spermatozoa and Y-bearing spermatozoa will be identified

from the density gradient fractions. Sperm suspensions will be smeared on slides for

FISH analysis using centromeric probes for chromosomes 18, X, and Y. The ratio of X- to

Y- chromosome bearing spermatozoa will be assessed as a percentage on at least 200

cells per slide. Aneuploid cells and those without signals will be omitted. Unselected

fractions of each sample will serve as controls. The rate of X-bearing spermatozoa

after 4-layer density gradient will be calculated. After thorough counseling, the

selected preconception gender specimen will then be utilized for assisted reproductive

fertilization- in vitro fertilization with or without intracytoplasmic sperm injection

(ICSI) or intra uterine insemination which are routine standard of care procedures.

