**Inclusion Criteria:**

Couples undergoing infertility treatment with IVF or insemination seeking gender specific offspring for medical and non medical reasons

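### The control specimen is not pinned down; if it means leftover gradient layers, any true enrichment is overstated by about 1/(1 − s), s being the share of sperm selected

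*Protocol*

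**What the plan says.** Section 1.1 sets the primary objective: to show that sperm of a given sex can be selected efficiently and reliably. Section 2.1 describes the laboratory work. A multilayer density gradient is run, and X- and Y-bearing sperm are identified "from the density gradient fractions". Slides are scored by FISH with probes for chromosomes 18, X and Y, on at least 200 cells per slide. "Aneuploid cells and those without signals will be omitted".

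The control is given in one sentence: "Unselected fractions of each sample will serve as controls". The next sentence says that the X-bearing rate after the 4-layer gradient will be calculated. The selected specimen then goes to IVF, with or without ICSI, or to insemination.

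The protocol does not say whether the control has been through the gradient. It mentions no aliquot set aside before layering, and it does not say that the whole ejaculate is layered. It lists volume and concentration for the semen sample but no sperm count per layer. Eligibility covers "Couples undergoing infertility treatment with IVF or insemination seeking gender specific offspring for medical and non medical reasons", without fixing which sex is sought.

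**The concern.** To show that selection is efficient, the X:Y mix of the specimen used for conception has to be compared with the man's own mix before processing. The leftover layers of the same gradient are not that baseline: X-bearing sperm drawn into the selected layer are missing from the rest, so the comparator moves away from baseline in the opposite direction. The contrast then exceeds the enrichment actually achieved, by an amount that depends on how much sperm the selected layer holds. The leftover control would also differ in make-up between couples seeking a girl and couples seeking a boy, if both are treated.

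This goes beyond a detail that a statistical analysis plan could supply later. The control is a physical specimen. If the whole ejaculate were layered and only percentages were scored per layer, the starting X rate could not be rebuilt, because that needs the number of sperm in each layer.

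**Working it through.** **Figures in the plan.** Section 2.4 gives 1000 couples, that is 1000 × 2 = 2000 subjects, and about 20% loss; 1000 × 0.80 = 800 couples if the loss applies to the 1000. The protocol gives no baseline X rate, expected enrichment, share of sperm per layer or standard deviation. Everything below on size therefore uses assumed values.

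**Step 1: the two readings side by side.** The only other use of the word *fractions* in section 2.1 is for gradient layers ("from the density gradient fractions"), and the product is called the selected specimen. In that sequence, unselected fractions are the layers not chosen. Against this, the control sentence attaches the word to each sample, and the section uses *sample* for what the man provides. A portion that never underwent selection fits that wording. The text does not settle it.

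**Step 2: mass balance.** Let b be the X rate in the raw sample, p_sel the rate in the selected layer, p_rem the rate in the pooled remaining layers, and s the selected layer's share of scorable sperm. With full recovery:

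b = s·p_sel + (1 − s)·p_rem, so p_rem = (b − s·p_sel)/(1 − s)

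p_sel − p_rem = (p_sel − b)/(1 − s)

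The true enrichment is p_sel − b. The inflation factor is 1/(1 − s), whatever the size of the enrichment.

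**Step 3: numbers** (assumed b = 50%, p_sel = 60%; true enrichment 10.0 points):

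| s | p_rem | Drop in the remainder (points) | Selected minus remainder (points) | Factor |
|---|---|---|---|---|
| 5% | 49.5% | 0.5 | 10.5 | 1.05 |
| 10% | 48.9% | 1.1 | 11.1 | 1.11 |
| 25% | 46.7% | 3.3 | 13.3 | 1.33 |
| 50% | 40.0% | 10.0 | 20.0 | 2.0 |
| 75% | 20.0% | 30.0 | 40.0 | 4.0 |

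For example, at s = 25%: p_rem = (0.50 − 0.25 × 0.60)/0.75 = 0.467.

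**Step 4: inert gradient.** If p_sel = b, then p_rem = b and the difference is 0 for every s. This control enlarges a real shift; it does not create one.

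**Step 5: does a large study protect against this?** Assume 800 men, 200 cells per slide, a true mean shift of 5 points, a between-man SD of the shift of 5 points, and the same s for every man. Binomial variance per slide near 50% is 50 × 50/200 = 12.5 squared points, so 25 for two slides.

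- Unprocessed control: mean 5.0, 95% half-width 1.96 × √((25 + 25)/800) = 0.49.
- Remainder, s = 25%: mean 5/0.75 = 6.7, half-width 1.96 × √((25/0.75² + 25)/800) = 0.58.
- Remainder, s = 50%: mean 5/0.50 = 10.0, half-width 1.96 × √((25/0.50² + 25)/800) = 0.77.

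In both remainder cases the interval excludes the true 5 points. Sample size narrows the interval around the wrong value.

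**The case against.** The strongest reply is that the control sentence speaks of each sample, not of the gradient, and that the section uses *selection* for the procedure itself. An unselected fraction of a sample is then a portion that did not undergo the procedure, which is the control one would want, and there is no bias. This stands as a legitimate reading. A reader might infer that the planned comparison does overstate enrichment; the protocol does not support that without condition.

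A reader might also infer that the leftover layers lose just what the selected layer gains. That is true of the excess number of X-bearing sperm, but not of the percentages that are scored. In the table above, a 10-point gain goes with a 1.1-point drop at s = 10%; the two are equal only at s = 50%.

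The following also stand:

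- The one quantity that the protocol says will be calculated, the X rate after the gradient, does not depend on the control, and no selected-minus-control difference is written down.
- The formula needs all leftover layers pooled and all sperm recovered and scorable. Lost sperm, omitted cells or the use of only some layers would change the size of the bias and could change its direction.
- The protocol does not say that the whole ejaculate is layered, so it cannot be said that the baseline will be lost.

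These replies limit the claim but do not remove it. The absolute post-gradient rate cannot by itself separate enrichment from a man's own starting mix, and the protocol names a control. A sentence that allows both an unbiased baseline and one inflated by 1/(1 − s) is badly fixed.

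**Conclusion.** The point holds as an ambiguity with a conditional bias. The control in section 2.1 can mean the unselected layers of the same gradient or an unprocessed portion of the ejaculate, and the text favours neither decisively. If leftover layers are used, a true enrichment is overstated by about 1/(1 − s): 1.1 at 10%, 1.3 at 25% and 2.0 at 50% of sperm selected. The values of s are assumed, with layers pooled and recovery complete. If an unprocessed portion is used, there is no such bias. On either reading an inert gradient gives no difference, so a false claim that the method works does not follow; what is at risk is the size of the enrichment reported. This is a cheap improvement, worth making before samples are processed because the right specimen has to be taken before layering.

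**What to change.** Replace the control sentence in section 2.1 with wording such as:

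> Before layering, an aliquot of the same unprocessed ejaculate is set aside, smeared and scored by the same FISH procedure. This aliquot is the control. Enrichment is the within-man difference in X/(X+Y) between the selected specimen and this aliquot. Gradient layers that were not selected are reported descriptively only.

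The cost is a small volume of semen, possibly one extra slide per man (none if the slide replaces a leftover-layer slide), and a reported enrichment that may look smaller. If an unprocessed aliquot is already what the laboratory takes, the change is one of wording only.

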**Inclusion Criteria:**

Couples undergoing infertility treatment with IVF or insemination seeking gender specific offspring for medical and non medical reasons

**Exclusion Criteria:**

Severe male factor

## 2.2 Rationale and Justification

Gender preselection has enormous implications for both animal and human reproduction. The human X chromosome is considerably larger than the Y, and thus the total DNA content of the haploid genome of an X-bearing spermatozoon is about 2.8% greater than that of a Y-bearing spermatozoon. The X chromosome's larger amount of DNA also enables it to carry numerous X-linked genes, many of which are of fundamental biological importance. Defective function of X-linked genes causes a wide variety of X-linked genetic diseases, of which haemophilia, Duchenne muscular dystrophy, and fragile X syndrome are prominent examples. In general, X-linked disorders are expressed only in males, and female carriers are protected from disease expression by the paired normal allele on their second X chromosome. Such carrier females transmit the genetic disorder to half, on average, of their male offspring. Preconception gender selection finds one important application in reducing the risk of having male children afflicted with a serious or fatal X-linked genetic abnormality.

The first and most widely used method for pre-conceptual gender choice of human babies was that of Ericsson (Ericsson et al., 1973; Beernink et al., 1993). The method was based on the passage of spermatozoa through columns of human serum albumin (HSA), and was founded upon the idea that Y-bearing spermatozoa swim faster than X-bearing spermatozoa. Passage through Percoll has also been used (Batzofin et al., 1995) as has a swim-up procedure (Check and Katsoff, 1993). These last two procedures, however, have not been confirmed by others. In our laboratory, we have attempted to perform hyperosmotic swelling followed by gel trapping (Kan et al., 2000) or by 2D gel electrophoresis (Bartsich et al., 2001). Flow cytometric separation of X- and Y-bearing spermatozoa was achieved in animals (Johnson et al., 1989) and led to weighting of the sexes in the animals’ offspring. The same method was used to separate human X- and Y-bearing spermatozoa (Johnson et al., 1993), and has been used more recently to determine the female sex in preventing X-linked disease (Levinson et al., 1995). However, flow cytometry is subject to the theoretical risks of exposure to the vital dye fluorochrome Hoechst 33342 and to a UV laser beam. Microsort (Schulman and Karabinus, 2005), the most successful method to date, claims to achieve a true enrichment of X-bearing cells at approximately 90%, but requires a major equipment investment and raises additional concerns about exposing sperm DNA to fluorescent staining and UV excitation.

Check, J.H. and Katsoff, D. (1993) A prospective study to evaluate the efficacy of modified swim-up preparation for male sex selection. Hum. Reprod., 8, 211–214.

## 2.3 Study Population

Subjects are health males and females who are undergoing infertility treatment. Subjects are not seriously of terminally ill.

## 2.4. Statistical Considerations

The total number of subjects recruited at WCMC will be 2000 with the expected

screen failure rate of about 20% due to drop out and inadequate samples. We plan to recruit 1000 couples (2000 subjects) for this research project.

# 3. Data Collection

## 3.1 Protected Health Information (PHI)

For the study, we will review medical history, embryology and medical information to include demographic Information, medication information, blood test results, ultrasound scan results, physical Examination Information and treatment outcomes. Data is recorded both electronically and in paper format and will be saved on a secure server on a password-protected computer or in a locked office. At the end of the study electronic identifiers will be deleted from the database and paper identifiers will be shredded.

## 3.2 Informed Consent

Informed consent will be obtained form both male and female partners in the clinical office of the Center for Reproductive Medicine by one of the fertility physicians or the research staff during their consultation. Subjects will be asked if they are interested in having their gametes (eggs and sperm) treated to help increase the chances of fertilization, particularly due to their previous history of failed fertilization with ICSI.

Potential subjects will be provided with study information and consent documents and will be given enough time to review the information and ask questions of the researchers.

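### The consent approach in section 3.2 describes a different intervention, purpose and population from the study in sections 1 and 2, and could mislead couples and misdirect recruitment

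*Protocol*

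**What the plan says.** Section 3.2 says that both partners give consent during their consultation. It then fixes the question put to them, which is whether they would like the study team's help with "having their gametes (eggs and sperm) treated to help increase the chances of fertilization". The ground it gives for putting this question to them is a specific treatment history: "particularly due to their previous history of failed fertilization with ICSI". Its next paragraph adds that candidates receive written study material and have time to read it and ask questions.

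The other sections describe a different project:

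- Section 1.1: "The primary objective of the study is to demonstrate the efficiency and reliability of selecting gender specific spermatozoa".
- Section 2.1, on the material processed: "Sperm samples will be provided by consenting males undergoing infertility treatment". The semen goes through a multilayer density gradient, and the fractions are read by FISH. The selected specimen is used, after counselling, for IVF with or without ICSI or for insemination.
- Inclusion criterion: "Couples undergoing infertility treatment with IVF or insemination seeking gender specific offspring for medical and non medical reasons".
- The only exclusion: "Severe male factor".

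**The concern.** Section 3.2 is the only place in the protocol that says what candidates are asked, and it is written as an instruction to staff. Staff who follow it would offer a benefit that the study is not designed to test and would leave out what the study does. The purpose matters to couples because the sex-selected specimen is then used for conception.

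Recruitment is also at stake. A question built around failed ICSI speaks to couples with that history. The inclusion criterion asks for something else, a wish for a child of a given sex, and it admits insemination couples, who may never have had ICSI.

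**Working it through.** No arithmetic applies: the protocol gives no figure on this point to reproduce. The check sets section 3.2 beside the sections that define the study.

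| Element | Section 3.2 | Sections 1.1 and 2.1 | Match? |
|---|---|---|---|
| What is treated | Eggs and sperm | Sperm only, by density gradient | No |
| Why | Better chance of fertilization | To "demonstrate the efficiency and reliability of selecting gender specific spermatozoa" | No |
| Who | Couples, particularly those with earlier ICSI failure | Couples having IVF or insemination who seek a child of a given sex | No |

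**Step 1, intervention.** Section 2.1 describes processing of semen only. No section describes any treatment of eggs.

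**Step 2, purpose.** The objective is sperm selection, and the only result that section 2.1 says will be calculated is the proportion of X-bearing sperm after the 4-layer gradient, with unselected fractions as controls. Section 3.1 lists embryology data and treatment outcomes among the records reviewed, so fertilization may be recorded. Recording it is not an aim to improve it, and no objective or comparison concerns it.

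**Step 3, population.** Neither the inclusion criterion nor the exclusion refers to earlier ICSI. Section 2.1 names insemination as one route for using the specimen: "ICSI) or intra uterine insemination which are routine standard of care procedures". Comparing the two descriptions gives three groups:

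- Couples with failed ICSI who do not seek sex selection fit the approach but fail the inclusion criterion.
- Couples seeking sex selection without an ICSI failure, including insemination couples, meet the inclusion criterion but are not the couples the approach describes.
- Couples with both features are eligible, but are told the wrong purpose.

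**Step 4, is there a reconciling passage?** Section 2.2 argues from X-linked disease and reviews earlier sperm-sorting methods. Section 2.3 describes healthy men and women in infertility treatment. Section 2.4 gives only recruitment numbers. None of these links the study to failed fertilization or to treatment of eggs.

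**The case against.** The strongest reply is that the sentence is carried-over text with limited practical effect, because other safeguards remain. Several parts of that reply stand.

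- **A reader might infer that consent is invalid.** The documents do not support this. The consent pages are not available for review and may describe the study correctly. Section 3.2 itself provides for written material and questions, and section 2.1 requires counselling before the specimen is used. Misdescription at this step is shown; failure of the whole consent process is not.
- **A reader might infer that the wrong couples are enrolled.** Section 3.2 is an approach, not an eligibility rule. The criteria in section 2.1 still apply, so a couple not seeking sex selection stays ineligible. The wording also makes ICSI failure a particular reason, not a requirement. What remains is a risk of misdirected invitations.
- **A reader might infer that the X/Y result is biased or will not generalise because semen after failed ICSI differs.** The protocol says nothing about such a difference. The unselected fraction of each sample is its own control, so a shift in who is approached does not by itself bias that within-sample contrast. This argument is not relied on here.
- **The recruitment target is not a count of harm.** The 1000 couples show how widely the step applies, not how many would be misinformed.

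None of this removes the contradiction. If the consent form is correct, it disagrees with section 3.2; if it repeats section 3.2, it disagrees with sections 1.1 and 2.1.

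**Conclusion.** The point holds as an internal contradiction. Section 3.2 disagrees with the objective, the intervention and the inclusion criterion, and nothing in the protocol reconciles them. The consequence is conditional: if staff follow the text, couples could be misled about purpose and benefit, and eligible couples could be passed over.

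The step covers every approach towards the planned 1000 couples (2 × 1000 = 2000 subjects). The size of the effect cannot be estimated from the document. The conclusion assumes only that section 3.2 is meant to be followed; it assumes nothing about the consent form or about semen quality. The correction should be made before the text is used, chiefly because of the misstated purpose.

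**What to change.** Reconcile section 3.2 with sections 1.1 and 2.1:

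1. Delete the wording on treatment of eggs, improved fertilization and earlier ICSI failure.
2. State instead that couples seeking a child of a given sex are asked whether the male partner's semen may be processed by the density gradient, analysed by FISH and used in their IVF/ICSI or insemination cycle. Say that the efficiency and reliability of the selection are what is being studied.
3. State which sex selection is offered. Section 2.1 identifies both X- and Y-bearing sperm in the fractions, but names only the X-bearing rate as a result to be calculated. This is for the sponsor to settle.
4. Confirm that the consent form matches the corrected text and does not carry the same wording.

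The cost is a one-paragraph amendment and a check of the consent form, with no added participants or procedures and no change to the design.

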## 3.3 Data Collection/Protection

All data will be saved electronically on a secure server or password-protected computer that only the study team will have access to.

## 3.4 REDCap

N/A

# 4. Tissue/Blood Usage

N/A

# 5. Collaboration

## 5.1 Internal Collaboration

Ronald O. Perelman and Claudia Cohen Center for Reproductive Medicine

## 5.2 External Collaboration

*N/A*

# 6. Additional Information

*N/A*
